### Plans to promote participant retention and complete follow-up

All investigators, including a specific study nurse, will promote participants retention and follow-up by using a team-work manner. A trial-specific information platform will be used. Follow-up data will be checked at least weekly. Loss of follow-up will be aggressively avoided by using multidisciplinary efforts.

## Outcome measures

### Primary outcome measure

The primary outcome measure is freedom from local progression (FFLP) [24]. FFLP will be defined as time with no in-field progressive disease. Response for target lesions will be defined according to the RECIST version 1.1 and modified RECIST (mRECIST) [52]. The target lesions should show intra-tumor arterial enhancement on contrast-enhanced CT or MRI and can be accurately measured in at least one dimension as 1 cm or more [53, 54].

Several tumor responses will be defined by two independent physicians (one hepatic-specific radiologist and one radiation oncologist): complete response (CR), total disappearance; partial response (PR), 30% decrease in single longest diameter (SLD) of contrast-enhanced part; stable disease (SD), neither partial response nor progressive disease met; and, progressive disease (PD), 20% increase of SLD or new lesion(s).

### Secondary outcome measure

Several secondary outcomes will be measured at 1 and 2 years, as follows: (1), overall survival; (2), progression-free survival; (3), tumor response rate; and (4), toxicity. Post-intervention complete or partial response will be defined as having a tumor response. Treatment-associated toxicity will be classified according to CTCAE, v.4.03 [55]. Toxicity within 3 months after initiation of interventions will be recorded as acute toxicity. And, toxicity that developed after 3 months will be considered as late toxicity. Liver-specific toxicity including classic and non-classic radiation-induced liver disease (RILD) will also be assessed. Degree of toxicities will be documented, such as ascites (i.e., absent, mild to moderate, and severe/refractory) and encephalopathy (i.e., absent, mild [I-II], and severe [III-IV]).

Several image and laboratory studies will be conducted for assessing treatment response and toxicities. First, CT, MRI, or abdominal sonography will be done per 3 months within the first two-year follow-up, then per 6 months thereafter for another 3 years. Second, specific laboratory studies will be followed up regularly, such as AST, ALT, and Bilirubin (both total and direct; Table 1). All adverse and potential harming events will be systemically collected and then analyzed in investigator meetings. Severe adverse events will be reported to IRB within 2 weeks as the IRB-monitoring guideline.

### Salvage management after SABR or re-TACE

For allocated patients who have incomplete response after SBRT or re-TACE, several re-salvage modalities will be evaluated as the following order: (1), surgical resection; (2), RFA; (3), TACE; (4), SABR; and, (5), conventional RT. Note that re-SABR or conventional RT may not be indicated for patients with post-SABR recurrence because of limitation of normal tissue tolerance.

### Data collection methods

Data will be collected primarily through the use of a paper-based case report forms (CRF), which will be completed by a specific study nurse and then confirmed by a physician. Subsequently, the data will be keyed in to the electronic research-incorporated database system (i.e., IROIP) that will be securely hosted at the Dalin Tzu Chi Hospital. Two independent investigators will be assigned to audit the process of data collection and correctness of the data. Baseline data will be collected routinely, including age, sex, ethnicity, education, economic, chronic hepatitis, prior treatments of HCC, and relevant medical comorbidities. All collected clinical data will be cross-linked with electronic laboratory data from the hospital HIS system.

### Sample size calculation

According to prior studies, response rates have been reported: 38% in patients treated with TACE alone [37] and 76.6% in those treated with TACE then salvage SABR [44]. As a result, an absolute increase of 30% in response rate will be considered as having a clinical significance. By using probability of type I error (α, 0.05; and, power [1 - β], 80%), 46 patients will be required in both the two study groups, resulting in a total study cases of 92. With an estimate of drop-out rate of 20%, we will enroll an additional 24 patients to counter potential attrition, reaching a final sample size of 120.

## Data management and access to data

All data collected in this study will be kept strictly confidential. All information from patients will be protected and stored in our data security system against unauthorized access. Only members in research can access to records, data, and samples. All information or data concerning the study will not be approached by any unauthorized third party.

## Data monitoring and auditing

During the whole study process, data accuracy and security will be monitored regularly by Data Safety Monitor Board (DSMB). All members of DSMB are independent from the sponsor and competing interests.

DSMB will perform planned interim analyses, and its members will decide whether the present trial should be terminated if stopping criteria are fitted. Stopping criteria include early identifications of significant benefits (i.e., between-group difference of absolute response rate > 30%) or harms (i.e., between-group difference of grade ≥ 3 toxicities > 20%). Final decision to stop the trial will require full agreement of all DSMB members.

Adverse events should be reported to the DSMB and IRB simultaneously, especially unexpected or severe adverse events. For every adverse event, potential avoidable etiologies will be checked systemically by both investigators and audit members of DSMB.

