## Statistical methods and data analysis

Data will be analyzed by using SAS (version 9.2; SAS Institute, Inc., Cary, NC, USA) and SPSS (version 17, SPSS Inc., Chicago, IL, USA), accordingly. Demographic data will be examined differences between groups by using chi-square test (for categorical variables) and Wilcoxon rank sum test (for continuous variables).

Time-to-event outcomes, such as FFLP (time to in-field target-tumor progression), progression-free (time to local, regional, or distance progression) and overall survival (time to patient death from any cause) will be evaluated by using Kaplan-Meier method. Curve difference between groups will be assessed by using log-rank test. Multivariate analysis will be done by using Cox proportional hazard regression. Hazard ratio with 95% confidence interval will be provided in conjunction with *p* values to demarcate effective size. All statistical analysis will be performed by using a two-tailed approach. A *p* value of < 0.05 will be considered as having a statistical significance.

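### The DSMB benefit rule stops on a fixed observed response difference equal to the design effect, on a week-6 secondary outcome, so the trial can end before FFLP is answered

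*Protocol article*

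**What the plan says.** Under Data monitoring and auditing: "DSMB will perform planned interim analyses, and its members will decide whether the present trial should be terminated if stopping criteria are fitted". The benefit criterion follows: "Stopping criteria include early identifications of significant benefits (i.e., between-group difference of absolute response rate > 30" percent. Harm has its own criterion, a toxicity difference. The section closes with "Final decision to stop the trial will require full agreement of all DSMB members".

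Under Sample size calculation the same 30 points is the design effect: "an absolute increase of 30% in response rate will be considered as having a clinical significance". The source rates are "38% in patients treated with TACE alone [37] and 76.6% in those treated with TACE then salvage SABR", and the result is 46 per group, raised to 120 in total for drop-out.

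Tumor response is listed under Secondary outcome measure, and Timing of assessments fixes its reading at week 6. The primary outcome is FFLP, given as a 1-year rate in the abstract and compared by log-rank test under Statistical methods and data analysis. That section also says "All statistical analysis will be performed by using a two-tailed approach" and that a p "value of < 0.05 will be considered as having a statistical significance", with no mention of the interim looks.

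**The concern.** A stopping boundary for benefit should demand strong evidence on the question the trial was set up to answer, and more of it when few patients have been observed. This rule does neither. The same 30 points applies at 12 or at 46 patients per arm. Because 30 points is also the effect the trial is designed to find, a trial that goes exactly to plan has roughly an even chance of meeting the rule at any look. The outcome is read at week 6, whereas the primary endpoint needs a year.

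A stop would leave FFLP, progression-free survival and overall survival immature. It would also report an exaggerated response difference, because only high observed values qualify. Repeated looks followed by an unadjusted final test can raise the false-positive rate for response.

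**Working it through.** **Inputs.** From the article: threshold above 30 points; control response 38%; design effect 30 points; two-sided 0.05; power 80%; 46 per group evaluable, 120 enrolled. Assumed: the alternative is 38% vs 68% (38 + 30); the look sizes are illustrative, because none is given.

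**The plan's own figure.** The standard two-proportion formula at two-sided 0.05 and 80% power gives 43 per group for 38% vs 68%, or 49 with continuity correction. For 46.6% vs 76.6% (30 points below the cited SABR rate) with correction it gives 47. The stated 46 therefore fits a 30-point difference, although the exact pair of rates is not stated.

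**Chance of meeting the rule at one look.** With X responders under re-TACE and Y under SABR, both binomial with n per arm, sum P(X = x)·P(Y = y) over all pairs with (y − x)/n > 0.30. The p-value for the smallest qualifying difference d uses z = d / √(2·p̄(1 − p̄)/n), with p̄ = (0.38 + 0.68)/2 = 0.53.

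| n per arm | smallest qualifying difference | its two-sided p | rule met, 38% vs 38% (SABR ahead) | rule met, 38% vs 68% | mean difference shown when met, 38% vs 68% |
|---|---|---|---|---|---|
| 12 | 4/12 = 33.3 pts | 0.10 | 7.0% | 52.6% | 44.9 pts |
| 15 | 5/15 = 33.3 | 0.067 | 4.4% | 50.8% | 43.8 |
| 20 | 7/20 = 35.0 | 0.027 | 1.6% | 44.1% | 43.5 |
| 23 | 7/23 = 30.4 | 0.039 | 2.4% | 55.5% | 40.1 |
| 30 | 10/30 = 33.3 | 0.010 | 0.5% | 45.1% | 40.8 |
| 46 | 14/46 = 30.4 | 0.003 | 0.2% | 53.0% | 37.5 |

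At 12 per arm a difference of four patients counts as significant benefit with p about 0.10, which the article's own 0.05 level would not call significant. With a true difference of only 15 points (38% vs 53%), a look at 23 per arm meets the rule about 18% of the time and then shows about 36 points.

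**How mature FFLP would be.** Assume uniform accrual of 120 patients over 36 months, 3.33 a month. Week-6 response on 46 patients is then available at 46/3.33 + 1.4 = 15.2 months. Patients with a full year of follow-up number (15.2 − 12) × 3.33, about 11. Over 48 months (the article also gives December 2020 as the end of recruitment) the rate is 2.5 a month, the time is 46/2.5 + 1.4 = 19.8 months, and the number is (19.8 − 12) × 2.5, about 19.

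**Overall error on response.** Simulation with 38% in both arms: the rule is met at any look, or the final two-sided chi-square test on response gives p < 0.05.

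| looks (per arm) | final n per arm | rule counted for benefit only | counted in either direction |
|---|---|---|---|
| none | 46 | 4.7% | 4.7% |
| 30 | 46 | 4.9% | 5.1% |
| 23 | 46 | 6.2% | 7.9% |
| 15, 30 | 46 | 8.4% | 12.2% |
| 10, 20, 30 | 46 | 9.8% | 14.9% |
| 12, 24, 36 | 46 | 11.0% | 17.3% |
| 30 | 60 | 5.3% | 5.6% |
| 15, 30, 45 | 60 | 8.8% | 12.6% |

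The result is sensitive to the exact look size. At 23 per arm a difference of 7 patients just qualifies; at 24 it takes 8, and one look at 24 of 46 gives about 5.4% (benefit only) or 6.0% (either direction).

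**The case against.** The strongest reply has four parts.

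First, the rule is not automatic. All DSMB members must agree, so the probabilities above are chances of meeting a criterion and upper limits on stopping. This stands: a reader might infer that the rule ends the trial, but the text supports only that it can. Unanimity does not mend the criterion, however, since the members would be voting on a threshold that takes no account of precision or of the primary endpoint.

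Second, a reader might infer that the trial's type I error exceeds 5%. The document does not support that. The error rates concern a final test of response. The outcome comparison the article names is the log-rank test, and no look at FFLP and no FFLP assumptions are given. Even for response, a single look at 30 per arm leaves the error close to nominal, and since the criterion is labelled as benefit, the lower, benefit-only figures are the more natural reading.

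Third, the number of looks, their timing and the alpha allocation commonly sit in an analysis plan or DSMB charter that is not shown. This also stands, and their absence is not the point. The article itself states the stopping endpoint and the threshold; a charter that followed it would inherit both, and one that departed from it would contradict it.

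Fourth, the article says the stopping criteria include these, so others may exist. Further criteria would not remove this one.

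**Conclusion.** The point holds as a fault in the rule as written. The benefit criterion is a fixed observed difference, equal to the design effect, on a secondary outcome read at week 6. Under 38% vs 68%, one look at 12 to 46 per arm meets it about 44–56% of the time with a mean observed difference of about 37–45 points. It can therefore stop the trial with the primary endpoint immature and the effect overstated. That conclusion does not depend on when the looks fall.

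The error inflation is conditional: about 5% for one look at 30 of 46 or 60 per arm, 6–8% for one look at 23 of 46, 8–12% for looks at 15 and 30, and 10–17% for three looks every 10 or 12 per arm. Each range runs from benefit-only to either direction. These figures assume 38% response in both arms and a final response test at an unadjusted 0.05. Nothing can be said about the size of the FFLP test.

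**What to change.** Delete the response-difference criterion for early benefit from Data monitoring and auditing, and from any DSMB charter that repeats it. Keep response as descriptive information for the DSMB.

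If an efficacy stop is still wanted, first state a planned number of FFLP events; the article has none, because the trial was sized on response. Then base the stop on the FFLP log-rank test with an O'Brien-Fleming-type (Lan-DeMets) boundary, and put the matching final significance level in Statistical methods and data analysis. With one look at half the planned events, the two-sided levels would be about 0.003 at the look and 0.049 at the end.

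The deletion costs an amendment and gives up an early stop on response. The boundary option also needs an FFLP event calculation and makes an early efficacy stop less likely.

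### The stated harm criterion is one fixed 20-point gap in pooled grade ≥3 toxicity, with no separate trigger for fatal or severe hepatic events, and a harm stop needs a unanimous DSMB

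*Protocol article*

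**What the plan says.** The section Data monitoring and auditing gives the DSMB planned interim analyses and says that "its members will decide whether the present trial should be terminated if stopping criteria are fitted". Two criteria follow. One is for "early identifications of significant benefits (i.e., between-group difference of absolute response rate > 30" percent, and the other is for "harms (i.e., between-group difference of grade ≥ 3 toxicities > 20" percent. Neither is tied to a number of patients, a look, or a measure of uncertainty. The section then adds: "Final decision to stop the trial will require full agreement of all DSMB members". That sentence does not distinguish stopping for harm from stopping for benefit.

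On reporting, the same section says: "Adverse events should be reported to the DSMB and IRB simultaneously, especially unexpected or severe adverse events". The section Secondary outcome measure adds: "Severe adverse events will be reported to IRB within 2 weeks as the IRB-monitoring guideline". It also fixes the grading scale ("Treatment-associated toxicity will be classified according to CTCAE, v.4.03 [55" in the reference list) and gives liver events special attention: "Liver-specific toxicity including classic and non-classic radiation-induced liver disease (RILD) will also be assessed". Ascites and encephalopathy are to be documented by degree. None of these events appears in the stopping criteria.

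**The concern.** A harm rule should respond to the events that matter most and should be easier to act on than a benefit rule. As published, this one falls short in three ways.

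- **Severity.** A fatal liver failure and a transient grade 3 laboratory value each add one event to the same count. The trial admits Child-Pugh A–B patients, and the section on Arm A foresees patients with poor liver function, so severe hepatic events are foreseeable.
- **Accrual.** The same gap applies however many patients have been treated, although its precision changes greatly over the trial.
- **Voting.** Unanimity is a defensible brake on stopping early for benefit. Applied to harm, it lets a single member keep the trial open after its own harm criterion has been met.

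At stake is whether the written rule would support the DSMB in acting on an excess of treatment deaths or severe liver events.

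**Working it through.** **Inputs from the article.** Harm threshold: strictly more than 20%, read here as percentage points, in parallel with the benefit criterion, which says absolute. Planned 60 per arm (sections on Arm A and Arm B), 1:1 allocation (Trial design). Toxicity graded by CTCAE.

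**Assumptions.** The article gives no toxicity rates, interim look sizes or operating characteristics for the rule, so there is no figure of its own to reproduce. I take grade 5 to mean death (CTCAE convention, not stated in the article). The look at 30 per arm is illustrative; 60 per arm is the planned total.

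**1. Largest one-sided excess that does not meet the criterion.** The rule needs (x_A − x_B)/n > 0.20.

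- n = 30: 6/30 − 0/30 = 20.0 points, not met; 7/30 = 23.3 points, met.
- n = 60: 12/60 − 0/60 = 20.0 points, not met; 13/60 = 21.7 points, met.

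These counts follow from the threshold alone. If all the events were deaths, the answer would be the same.

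**2. Strength of evidence at those counts.** With all events in one arm and equal arms, the two-sided Fisher p-value is 2 × C(n, k)/C(2n, k).

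- 6/30 v 0/30: 2 × C(30,6)/C(60,6) = 2 × 593,775/50,063,860 = 0.024.
- 12/60 v 0/60: 2 × C(60,12)/C(120,12) = 0.0003.

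**3. Pooling of grades.** Suppose 6/30 in each arm have grade ≥3 toxicity, but 3 of the 6 in one arm are fatal and none in the other. The gap is 6/30 − 6/30 = 0 points, so the deaths cannot move the criterion.

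**4. Dependence on accrual.** Take an observed 30% v 10%, exactly at the threshold. The approximate 95% interval is 20 ± 1.96 × 100 × √[(0.3×0.7 + 0.1×0.9)/n] points.

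| n per arm | counts | 95% interval for the gap (points) |
|---|---|---|
| 20 | 6 v 2 | −4.0 to 44.0 |
| 30 | 9 v 3 | 0.4 to 39.6 |
| 60 | 18 v 6 | 6.1 to 33.9 |

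The same observed gap is compatible with no excess at 20 per arm and clearly excludes zero at 60, yet the rule treats the two alike.

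**5. Illustrative chance of meeting the criterion (SABR worse; exact binomial, P[(x_A − x_B)/n > 0.20]).** The true rates are assumed.

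| True grade ≥3 rates | 20 per arm | 30 per arm | 60 per arm |
|---|---|---|---|
| 10% fatal v 0%, no other grade ≥3 events | 4.3% | 2.6% | 0.6% |
| the same excess on a 10% background (20% v 10%) | 13% | 10% | 5% |
| 30% in both arms | 6% | 3% | 0.6% |

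A true 10-point excess of deaths lies below the threshold, so more data make the criterion less likely to be met.

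**6. Voting.** No calculation is needed. If all must agree, one disagreement prevents the stop, and the sentence makes no exception for harm.

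**The case against.** The strongest reply is that this is a journal article. Look timing, death-specific triggers and formal boundaries usually sit in a DSMB charter or full protocol. The list of criteria is introduced as inclusive, so others may exist. Grade 5 events do count within grade ≥3. Adverse events go to the DSMB and IRB at the same time, each is checked for avoidable causes, and severe ones reach the IRB within two weeks. A run of 6 or 12 deaths against none would hardly go unnoticed.

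Most of this stands, and it limits the point. A reader might infer that deaths are ignored, that the 20-point gap is the only ground on which the trial can ever stop, or that patients are unprotected. The documents do not support any of these. Deaths are counted but carry no extra weight, the list is not closed, and there is a reporting route.

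A reader might also take the rule's performance at a true 30% v 10% as proof of insensitivity. That scenario sits on the threshold, where any fixed-gap rule is met roughly half the time. At 40% v 10% it is met 72%, 79% and 89% of the time at 20, 30 and 60 per arm. Chance triggering under equal rates is also modest in the SABR-worse direction beyond very small looks. Nor can one put a number on how often unanimity would fail, since the article gives no board size and members deliberate together.

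The reply does not remove what the article states. It defines harm by one pooled gap, makes the termination decision conditional on the criteria, attaches no stopping consequence to individual reports, and requires unanimity for a harm stop. These are provisions on the page, not omissions. A per-arm toxicity ceiling or a formal sequential or Bayesian boundary, by contrast, would be a design preference, and its absence is not an error.

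**Conclusion.** The point holds as a should-fix. The stated harm criterion is a single gap of more than 20 points in pooled grade ≥3 toxicity, the same at every accrual, with no separate trigger for fatal or severe hepatic events. Treatment deaths of 6/30 v 0/30 (p = 0.024) or 12/60 v 0/60 (p = 0.0003), with no other difference in grade ≥3 events, would not meet it. When it is met, one member can veto the stop.

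The counts rest only on the threshold, read as percentage points. The probabilities in step 5 of the working rest on assumed rates and look sizes and are illustrations. The veto follows from the wording. It is not a must-fix, because deaths are counted and reported and the list of criteria is left open. The written rule gives the DSMB poor support for acting on harm, but it does not prevent the DSMB from seeing it.

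**What to change.** Amend the section Data monitoring and auditing, and the DSMB charter if there is one, in three ways:

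1. Limit the unanimity requirement to stopping for benefit. For harm, let a majority DSMB recommendation suffice.
2. Add a separate trigger for ad hoc DSMB review of grade 5 events and of grade 4–5 hepatic events, with the level set in advance by the DSMB. This would also give the adverse-event reports already sent to the DSMB a stated consequence.
3. State that the 20-point gap is a guideline, to be read with its confidence interval at the accrued sample size, and is not a necessary condition for stopping.

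The cost is wording and IRB re-approval of the change. The data are already collected under the existing CTCAE and liver-toxicity assessments, and the sample size is unaffected. The downside is a slightly higher chance of an unnecessary pause.
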